### Study design

We will conduct a 2×2 factorial, randomised, and open label trial to evaluate the specific effects of physical activity and behavioural therapy in reducing mortality and hospitalisation in HF patients in India. The patients recruited in the study will be randomly assigned to one of four intervention groups: a control arm (usual care-C), intervention A (physical activity), intervention B (cognitive behaviour therapy), and a combination of intervention A and B (physical activity + cognitive behaviour therapy)
^
19
^. We assumed no interaction between the treatment arms. 

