### Sample size

Assuming a three-year cumulative event rate of 50% or more for the primary outcome (mortality)
^
39
^, it was estimated that a sample size of 1632 participants would provide 80% power to detect at least 20% relative risk reduction of the primary outcomes for each of the randomised comparisons.

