### Randomisation and blinding 

Treatment allocation at each site will be assigned using an automated randomization process developed by an independent person who is not involved in the study. Computer-generated random numbers will be used for randomisation into four groups. Units of randomisation will be HF patients attending the outpatient department of the selected hospitals. Consenting participants will be allocated to one of the four groups (three intervention groups or one usual care group) in a 1:1:1:1 ratio using a central randomisation system. Randomisation will be stratified by site. The randomisation listing will be attached to the
REDCap system for automatic online randomization upon completion of screening and collection of all baseline data. The trial is open-label, and patients and investigators will be aware of treatment allocation.

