### Statistical analysis

Baseline characteristics and follow-up measurements will be described using descriptive summary measures depending on the level and scale of measurements. Intention to treat analyses will be performed. The effects of intervention on the primary mortality endpoints will be estimated from unadjusted Cox proportional hazard models. We will combine mortality and hospitalisation for HF as a composite secondary outcome. To analyse the composite outcome, in participants with more than one outcome event during follow-up, survival time to the first relevant endpoint will be used in the analysis. As a general practice, all participants will be censored at their date of death or, for those still alive at the end of follow-up, or at the date of their last visit. Patients with an unknown vital status will be also right censored when they were last known to be alive. To calculate the relative risk reductions, we will use the formula based on the hazard ratio ([1–hazard ratio] ×100). The reciprocals of the absolute risk differences with their normally approximated 95% confidence intervals (CIs) will be calculated as the numbers needed to treat. For the continuous secondary outcomes variables, differences between randomised groups during follow-up will be estimated from linear mixed models or generalised estimating equations (GEE) as appropriate. In general, all p values will be calculated from two-tailed tests of statistical significance with a Type I error rate of 5%.

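### The protocol uses relative risk reduction for two different quantities, so the power for a 20% effect depends on a scale and a contrast it does not state; separately, the NNT interval rule fails when the risk difference CI includes zero

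*Protocol article*

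**What the plan says.** **Sample size section.** The planning input is a cumulative risk: "Assuming a three-year cumulative event rate of 50% or more for the primary outcome (mortality"). The section claims 80% power for a total of 1632 and describes the detectable effect this way: "to detect at least 20% relative risk reduction of the primary outcomes for each of the randomised comparisons". It does not print the event rate under treatment, the test used, or whether a comparison is one arm against another or one factor level against the other.

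**Statistical analysis section.** Mortality is analysed with an unadjusted Cox model, and the same term is then tied to that model: "To calculate the relative risk reductions, we will use the formula based on the hazard ratio", namely one minus the hazard ratio, times 100. For absolute effects it adds: "The reciprocals of the absolute risk differences with their normally approximated 95% confidence intervals (CIs) will be calculated as the numbers needed to treat". Tests are two-sided at 5%.

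**Design.** Patients are allocated "in a 1:1:1:1 ratio using a central randomisation system" to the four cells of a 2 × 2 factorial. The Study design section adds: "We assumed no interaction between the treatment arms".

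**The concern.** A relative risk reduction compares the proportions who die by a given time. One minus the hazard ratio compares death rates among those still alive. The two nearly agree when deaths are rare and separate when deaths are common, and this trial expects at least half of patients to die within three years. Under proportional hazards, a beneficial treatment always has 1 − HR larger than the relative reduction in cumulative risk.

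Two things are at stake. The first is the headline result: readers may take the reported percentage as the share of three-year deaths avoided, when it is larger than that share. The second is the power statement: a 20% effect on one scale is not a 20% effect on the other, so the effect for which the trial has 80% power is not defined.

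The NNT rule raises a separate, smaller problem. The reciprocal function breaks at zero, so inverting the two limits of an interval that contains zero does not give an interval for the NNT.

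**Working it through.** **Inputs from the protocol.** Control three-year mortality 50%; effect 20%; power 80%; two-sided 5%; total 1632 in four equal groups, so 408 per group and 816 per factor level. **Assumptions.** Proportional hazards, so treated risk = 1 − 0.5^HR; Schoenfeld's formula for log-rank or Cox power; complete three-year follow-up.

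**1. Reproduce 1632.** Compare 50% with 40% (risk ratio 0.80), pooled proportion 0.45:
- n = [1.960 × √(2 × 0.45 × 0.55) + 0.842 × √(0.25 + 0.24)]² / 0.10² = 387.3 per group.
- With continuity correction: (387.3 / 4) × [1 + √(1 + 4 / (387.3 × 0.10))]² = 407.1, so 408.
- 4 × 408 = **1632**, an exact match.

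Without the correction the total is 4 × 388 = 1552. Planning on HR 0.80 at the margins gives about 1363 to 1488, depending on the formula and on whether the other factor works. That reaches roughly 1632 only with about 10–15% dropout, which the protocol does not state.

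**2. Translate between the scales.**

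| True effect | Treated three-year risk | Relative reduction in risk | Reported by the (1 − HR) formula |
|---|---|---|---|
| Risk ratio 0.80; HR = ln 0.6 / ln 0.5 = 0.737 | 40.0% | 20.0% | 26.3% |
| HR 0.80 | 1 − 0.5^0.8 = 42.6% | 1 − 0.4257 / 0.5 = 14.9% | 20.0% |

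**3. Power at N = 1632.** Power = Φ(√D × \|ln HR\| / 2 − 1.960), with D the expected deaths in the comparison.

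| Contrast | HR 0.80 | HR 0.737 |
|---|---|---|
| One arm v one arm, 408 v 408 | D = 408 × 0.9257 = 378; **58%** | D = 408 × 0.90 = 367; **83%** |
| Margins, 816 v 816, other factor inert | D = 755; **87%** | D = 734; **98%** |
| Margins, both factors at HR 0.80 | D = 698; **84%** | – |

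Example, top left: √377.7 × 0.2231 / 2 = 2.168; Φ(2.168 − 1.960) = 0.58.

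For 80% power at HR 0.80, the deaths needed in each comparison are 4 × (1.960 + 0.842)² / 0.2231² = 631. Pairwise, that is 631 / 0.9257 = 682 per arm, or about 2,730 in all.

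The protocol allows mortality above 50%. Pairwise power at HR 0.80 is then 62% at 55% mortality, 66% at 60% and 73% at 70%, so it stays below 80% across that range.

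**4. NNT rule.** As an illustration with an assumed result, take 50% v 47% and 816 per group:
- SE = √(0.5 × 0.5 / 816 + 0.47 × 0.53 / 816) = 0.0247.
- 95% CI for the difference: 3.0 ± 4.8 points, that is −1.8 to 7.8.
- Point estimate of the NNT: 1 / 0.03 = 33.
- Reciprocals of the limits: −54 and 12.7.

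Read as an ordinary interval, −54 to 12.7 excludes its own estimate of 33. It also includes values between −1 and 1, which no NNT can take.

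**The case against.** **Power.** A reader might infer that the trial has only 58% power on its own measure. The documents do not support that. The figure needs two readings together: that each comparison is one arm against one arm, and that 20% means HR 0.80. The protocol states no pairwise analysis. A 2 × 2 factorial with no assumed interaction, and the stated aim in the Conclusions of learning whether each component works independently, fit analysis at the margins. There the same 1632 gives 84–87% at HR 0.80. Three of the four combinations of scale and contrast meet the stated 80%. This objection stands, and the shortfall is conditional.

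**Planning scale.** The 40% rate and the test are not printed, so planning on the risk scale is an inference. That also stands, although an exact match with no added input is better evidence than a near match that needs an unstated dropout.

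**Label.** The formula is given openly, and the hazard ratio, its interval and its p value are unaffected. This limits the harm but does not remove it: the name does not fit the quantity, and the same name carries the power claim.

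**NNT.** Two stronger readings fail. One is that the plan would report an NNT of 10 where 13.5 is right. It would not: the NNT comes from the absolute risk difference, and 50% v 42.6% yields 1 / 0.0743 = 13.5 under the plan's own rule. The other is that crude proportions will be used despite censoring. The protocol does not say so, and the estimator and time point are details that an analysis plan commonly supplies. What remains is the inversion of an interval that includes zero, which the stated rule does not handle.

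**Conclusion.** The concern holds as an inconsistency of scale. The sample size and analysis sections give one name to two quantities that differ materially at 50% mortality: the effect that reproduces 1632 is a 20% reduction in three-year risk but would be reported as 26%, and an effect reported as 20% is a 14.9% reduction in that risk. These figures rest on proportional hazards and 50% control mortality. The size of the mismatch does not depend on the contrast.

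No printed number is shown to be wrong: 1632 reproduces, and a Cox analysis of the effect behind it has at least 80% power even pairwise. What is undefined is the effect and the contrast to which the 80% applies, and the plausible readings run from about 58% to about 98%. Power falls short only if pairwise comparisons and HR 0.80 are both intended.

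The NNT rule is invalid whenever the confidence interval for the risk difference includes zero. This affects a descriptive statistic and not the primary test.

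**What to change.** 1. State the target effect as a hazard ratio (0.737 if a 20% reduction in three-year risk was meant, 0.80 if a 20% reduction in hazard was meant). Give the required number of deaths and say whether it applies at the factorial margins or between single arms. Restate the power on that basis.
2. Call 1 − HR a hazard reduction. Beside it, report the three-year risk ratio and risk difference from Kaplan-Meier estimates.
3. Take the NNT from that risk difference. Where the interval for the difference includes zero, give the risk difference only, or an NNT interval split through infinity (in the illustration, benefit from 12.7 to infinity and harm from 54 to infinity).

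The cost is wording and a little extra analysis, with no change to data collection. The stated power will look less favourable if pairwise comparisons at HR 0.80 are what the investigators intend.

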### Monitoring arrangements

The trial will be monitored by the data safety management board (DSMB). This will be an on-going activity from the time of initiation until trial close-out and will comply with the principles of Good Clinical Practice (GCP) and applicable regulatory requirements. The DSMB will monitor the overall conduct of the study to ensure the validity and integrity of the study findings, and will meet annually. The DSMB will comprise independent members with at least one statistician and one practicing cardiologist.

### Adverse events

All adverse events (AEs) that are directly observed and spontaneously reported by the research nurse and will be recorded in the CRF and reported to institutional ethics committee of the concerned hospital and coordinating centre. Death is considered as the serious adverse event in this study.

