## Abstract

**Background:** Heart failure (HF) is a multi-morbid chronic condition, which adversely affects the quality of life of the affected individual. Engaging the patient and their caregivers in self-care is known to reduce mortality, rehospitalisation and improve quality of life among HF patients. The PACT-HF trial will answer whether clinical benefits in terms of mortality and hospitalisation outcomes can be demonstrated by using a pragmatic design to explore the specific effects of physical activity, and cognitive behavioural therapy in HF patients in India.

**Methods:** We will conduct a 2
× 2 factorial, randomized, open-label trial, which aims to see if rehabilitation strategies of structured physical activity training and cognitive behavioural therapy for depression and self-management reduce the risk of repeat hospitalisation and deaths in HF patients in India. Patients will be randomised to (1) physical activity + usual care (2) cognitive behaviour therapy + usual care, (3) physical activity + cognitive behaviour therapy + usual care, and (4) usual care at 1:1:1:1 ratio. Time to mortality will be the primary outcome. A composite of mortality and hospitalisation for HF will be the main secondary outcome. Additional secondary outcomes will include ‘days alive and out of hospital’, cumulative hospitalisation, quality of life, Minnesota Living with Heart Failure questionnaire score, depression score, six minutes walking distance, handgrip strength, and adherence to medicines and lifestyle.  The effects of intervention on the primary outcome will be estimated from Cox proportional hazard models. For the continuous secondary outcome variables, differences between randomised groups will be estimated from linear mixed models or generalised estimating equations (GEE) as appropriate.

**Discussion:** PACT-HF is designed to provide reliable evidence about the balance of benefits and risks conferred by physical activity and cognitive behavioural therapy-based cardiac rehabilitation for those with HF, irrespective of their initial disease severity.

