### Intervention and comparator

Intervention A (physical activity and usual care): Participants will be asked to perform physical activity, along with a structured exercise program of moderate intensity for at least 30 minutes, five days a week throughout the study period.

Intervention B (cognitive behaviour therapy and usual care): Participants will receive individual face-to-face behavioural therapy sessions once a month and telephone sessions once every week.

Intervention C (physical activity + cognitive behaviour therapy and usual care): Participants will receive both behaviour therapy intervention and exercise regime.

Comparator: Participants in the usual care arm will continue without any intervention as suggested above.

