### Structured physical activity intervention

After the randomisation, the structured physical activity intervention group will receive face-to-face group training sessions by the research nurse in the outpatient settings of the respective study sites. All the intervention participants will be advised to participate in the group session. They will be asked to perform all their activities of daily living, regular physical activity (
*e.g.*, walking, gardening, and household work) along with their exercise of choice. Participants will be informed to engage in mild to moderate exercise for at least 30 minutes, five days a week. The exercise component will be demonstrated over 10 sessions and will include a warm-up and a cool-down session. The participants will be requested to increase the duration of the exercise session according to their tolerance. Yoga-based physical activity will be also introduced as part of the intervention. Very simple and specific yogasanas will be demonstrated to HF patients to increase their overall physical activity.

The participants will be instructed to perform each schedule of exercises and will be asked to increase the intensity gradually every month. The type and duration of exercises will change with the intensity of the exercise that they perform. All participants receiving the exercise training will be given a manual developed in Malayalam (native language) with all instructions. Further, a self-assessment checklist will be provided to capture the fidelity to the intervention regime (
*Extended data*)
^
25
^

Participation in the intervention session will be monitored using self-assessment forms. Participants will be asked to bring these self-assessment forms at each follow-up visit. A mobile phone application (containing the app Metronome Beats) will be used by patients to increase the intensity and duration of exercise. The research team will contact participants weekly through telephone and provide input on modifying and tailoring the exercise intensity and duration. 

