### Cognitive behavioural therapy intervention

The cognitive behavioural therapy modules developed for the study will be simple, easy, and understandable such that the intervention can be given even by even a lay person. The behavioural therapy intervention will consist of individual sessions of 30–45 minutes duration, that will be delivered by a trained nurse. The sessions will be given in the outpatient settings of the study sites. We will use a detailed trainer’s manual to explain the sessions to the research nurse. The delivery of the brief behavioural counselling sessions will be based on a structured guidance document. Participants will receive individual face-to-face sessions once a month and telephone sessions once a week for the next 10 months. The cognitive behavioural therapy sessions will generally involve building rapport with patients, understanding patient’s thoughts and belief about HF, assessing their dysfunctional thoughts, teaching them methods to cope with the disease, incorporating positive thoughts, teaching them methods to relax the mind and reviewing the assignments given to each individual patient. At the end of each session, participants will be required to complete the ‘Mood thermometer
^
26
^’ to see how they feel each day and their mood changes throughout the therapy.

All participants receiving the cognitive behavioural therapy interventions will be given a behavioural therapy manual in their native language. This self-help manual will aid in guiding the participants in unsupervised home tasks and assignments based on behavioural therapy. A self-assessment checklist (
*Extended data*)
^
27
^ will be provided and it will help the participants in monitoring their progress and in attaining therapy-related goals during the follow-up periods.

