### Measurements

The socio-demographic details like age, gender, education, occupation will be recording during the patients’ first visit. Aetiology, history and risk factors for the disease will also be recorded at baseline. Furthermore, recent blood investigations done in the three months prior will be also analysed.

Participants will be seen every three months until the end of the three-year follow-up
^
28
^ will help to identify measurement details at different time points. At study visits, depression and anxiety scores will be collected from each participant by using the PHQ9
^
29
^ and GAD-7
^
30
^ questionnaires, respectively. The self- management component will include assessments of participant’s medication adherence, management of weight and diet, and family support as reported by the patient. The medication adherence will be measured using the four-item Morisky Green Levine medication adherence scale
^
31
^. We will use the multimorbidity treatment burden questionnaire (MTBQ)
^
32
^, to measure treatment burden. The study proforma will also assess the medical utilisation, patient satisfaction in quality of care, family support, and diet management.

We will use the Kansas City Cardiomyopathy Questionnaire (KCCQ)
^
33
^ and EQ-5D-5L
^
34
^ to assess quality of life. The KCCQ assess the disease specific quality of life. The EQ-5D-5L provides a simple descriptive profile and a single index value for health status. Standardized and validated instruments will be used for assessing the functional status, severity of disease, and treatment.

The six-minute walk test (6MWT) will be measured using standard settings during their out-patient visits
^
35
^. The 6MWT will be performed indoors, on a flat-surface corridor, which is 30 m long. Before starting the test, the research nurse will record the blood pressure, pulse rate, and oxygen saturation. The patient will be advised to start the test after being instructed on the test procedure. The test will run for six minutes and will follow all the instructions given by the American Thoracic Society
^
36
^. At the end of the test, the distance covered will be documented along with the pulse rate, blood pressure, oxygen saturation and Borg’s rating of perceived exertion and fatigue.

Hand grip strength will be assessed using standard assessment procedures using a dynamometer
^
37

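### The serious adverse event category holds only death, and other events are collected passively under unequal contact, so the plan is poorly equipped to support its claim about risks

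*Protocol article*

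**What the plan says.** The Adverse events section fixes the serious category in one sentence: "Death is considered as the serious adverse event in this study". For everything else, the events to be recorded and reported are described as "All adverse events (AEs) that are directly observed and spontaneously reported by the research nurse". They go into the CRF, to the ethics committee of the hospital concerned and to the coordinating centre. No scheduled or solicited enquiry is stated.

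The Abstract says the trial is "designed to provide reliable evidence about the balance of benefits and risks conferred by physical activity" and CBT-based rehabilitation, whatever the initial severity of disease.

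Planned contact differs by arm:

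- **All arms** (Measurements): "Participants will be seen every three months until the end of the three-year follow-up".
- **Physical activity** (Structured physical activity intervention): ten demonstration sessions, and "The research team will contact participants weekly through telephone". How long the calls continue is not stated.
- **CBT** (Cognitive behavioural therapy intervention): monthly face-to-face sessions and "telephone sessions once a week for the next 10 months".
- **Usual care** (Intervention and comparator): "Participants in the usual care arm will continue without any intervention as suggested above".

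The trial is open-label (Randomisation and blinding). The research nurse who delivers the intervention (Intervention delivery) is also the person named as reporting adverse events.

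**The concern.** There are two weaknesses, and each makes the other worse.

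First, a serious category that contains only death repeats the primary outcome. An arrhythmia, a syncope or an injurious fall during exercise would be an ordinary adverse event at most, whatever its consequences.

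Second, passive reporting finds events in proportion to the opportunities to mention them. Here those opportunities depend on the randomised arm, and both participant and nurse know the arm. A between-arm difference in non-fatal events could then reflect who was telephoned rather than who was harmed. It could make exercise look more harmful than it is, or make a real excess impossible to interpret.

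At stake is the safety half of the abstract's claim. The mortality comparison is not affected.

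**Working it through.** **1. The plan's own figure.** The Sample size section gives 1632 participants. A two-proportion calculation with 50% v 40%, two-sided 5%, 80% power and continuity correction gives 408 per arm, and 4 × 408 = 1632. Exercise is assigned in two of the four arms: 2 × 408 = 816, against 816 without exercise. The Adverse events section itself gives no figure.

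**2. What the serious category adds.** Outcome measures makes time to mortality the primary outcome. The serious category is death. Harm information beyond the primary outcome: none.

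**3. What the other outcomes capture.** Outcome measures also lists HF hospitalisation (in the composite), cumulative hospitalisation rate and days alive and out of hospital, in every arm. A harm that leads to admission is therefore partly counted. Not covered are serious events without admission, the classing of any admission as serious, and any stated link in time to exercise.

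**4. Planned contacts per participant over three years.**

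- Visits, all arms: 36/3 = 12.
- CBT calls over 10 months: 10 × 52/12 ≈ 43. Monthly sessions: 10. CBT-only total: 43 + 10 + 12 = 65, assuming that sessions and visits do not coincide.
- Usual care: 12. CBT-only against usual care: 65/12 ≈ 5.4.
- Exercise, if calls last 10 months (assumption): 43 + 12 = 55. If they last three years (assumption): 156 + 12 = 168. The demonstration sessions are left out.

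In a factorial trial the exercise comparison sets 816 against 816, and half of those without exercise receive CBT:

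- Mean contacts without exercise: (12 + 65)/2 = 38.5.
- Ratio: 55/38.5 ≈ 1.4 to 168/38.5 ≈ 4.4, taking the combined arm to have the same contacts as exercise alone.
- If the combined arm's CBT contacts (43 + 10 = 53) are additional and exercise calls last three years: [(168 + 221)/2]/38.5 ≈ 5.1.

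Intervention delivery gives one year for the CBT sessions, not 10 months; the two sections should be reconciled. One year gives 52 + 12 + 12 = 76 contacts and a mean of (12 + 76)/2 = 44 without exercise. The ratio is then (52 + 12)/44 ≈ 1.5 (exercise calls also for one year) to 168/44 ≈ 3.8. The conclusion does not change.

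**5. How far direct observation reaches.** Exercise is asked for on five days a week throughout the study: 5 × 52 × 3 = 780 sessions over three years. Ten are demonstrated: 10/780 ≈ 1.3%. Most exercise would take place unobserved.

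**6. What uneven detection can do (illustration).** The detection shares are assumptions; the documents give none. With equal true risk, the apparent risk ratio is the ratio of detection shares:

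- 90% in the three contacted arms and 60% in usual care: the non-exercise half averages (90 + 60)/2 = 75%, so 0.90/0.75 = 1.2.
- 90% v 60% at the exercise comparison itself: 1.5.
- 60% v 90%, the reverse: 0.67.

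The chance of a nominally significant false difference is the power of a two-sided 5% two-proportion test, 816 v 816, at the detected risks:

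| True risk, both groups | 90% v 75% found | 90% v 60% found |
|---|---|---|
| 5% | 11.5% | 35.7% |
| 10% | 19.5% | 63.4% |
| 20% | 37.2% | 92.5% |

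The 90% v 60% column is the harsher case: if CBT participants are detected at 90%, it needs usual care at only 30%.

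**The case against.** **Harm is not invisible.** Three hospitalisation outcomes are collected in every arm, two of them not restricted to HF in the text, and Measurements adds medical utilisation. A reader might infer that the trial cannot say anything about risk. The documents do not support that; the gap is in non-admitted events, classification and attribution.

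**Spontaneous report is not the only route.** Direct observation is named too, and a non-fatal arrhythmia or fall is still recordable as an adverse event. This stands, although step 5 shows that little exercise would be observed.

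**Direction.** A reader might infer that harms of exercise would be undercounted relative to the other arms. More contact points the other way: more events found in the active arms and more missed in usual care.

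**Size.** A reader might divide 52 weekly calls by 4 visits a year and infer a 13-fold imbalance. That fails. CBT calls last 10 months, the duration of the physical activity calls is not stated, contacted arms also attend the visits, and half of the non-exercise group receives CBT.

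**Unseen material.** This is a condensed article. The follow-up form, which may contain an event checklist, and the tables for the DSMB are not shown. That limits what can be said about solicitation and DSMB content. It does not reach the death-only sentence, which a fuller document could widen only by contradicting it.

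**Where the claim sits.** The benefits-and-risks wording is in the Abstract; the main Discussion and Conclusions speak of survival and quality of life. True, but the Abstract states it as what the trial is designed to provide.

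**Conclusion.** The point holds as a mismatch between the safety plan and the stated aim. The death-only category is fixed by the text and adds nothing to the primary outcome. Passive collection with unequal contact in an open-label trial would find non-fatal events unevenly, probably more often in the active arms.

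On the assumptions in the working, the contact imbalance at the exercise comparison is about 1.4 to 4.4, or about 5 if the combined arm's contacts add up. It affects the comparison of 816 with 816. How far this distorts event rates cannot be derived from the documents; the illustration gives apparent risk ratios of 1.2 to 1.5 with no true difference if more events are found with exercise.

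As described, the plan is poorly equipped to support the claim on risks. Admission-related harm is partly captured, and the mortality analysis is untouched. The part about solicitation assumes that the unseen follow-up form does not already ask about events in the same way in every arm. The change is worth making, but the main result does not depend on it.

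**What to change.** 1. Widen the serious category to include non-fatal events: life-threatening events, unplanned hospitalisation and lasting disability. Add a flag for timing relative to exercise.
2. At the existing three-monthly visits, ask about events since the last contact with the same checklist in all four arms.
3. Base the main between-arm safety comparison on these solicited events together with deaths and hospitalisations, including those in participants who die or drop out before their next visit. A comparison limited to visit reports would lose the latter, which matters with an assumed three-year mortality of 50% or more.
4. Report spontaneously reported events separately.
5. Give counts by arm to the DSMB.

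The cost is one CRF page, a few protocol sentences and more reports to process. The extra load should not be dismissed: a dedicated nurse at each of six hospitals delivers the intervention and enters the data, for an average of 1632/6 = 272 participants per centre. Randomisation, sample size and the primary analysis do not change, and no visits are added.
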